### Analysis

#### Analysis of the primary outcome measure

The primary outcome—number of bronchiectasis exacerbations per participant requiring antibiotics over 12 months—will be compared between randomised groups using negative binomial regression adjusted for stratification factors. This model will be used to compute CIs to test the superiority and non-inferiority hypotheses. The two-sided 95% CI for difference in mean number of exacerbations per year between the combination of LAMA/LABA and ICS/LAMA/LABA compared with placebo will be found: the placebo versus LAMA/LABA hypothesis will be rejected if the upper limit is lower than 0. We will estimate the difference between LAMA/LABA and ICS/LAMA/LABA arms on the relative scale using the incidence rate ratio, and test whether the upper boundary of the two-sided 90% CI is lower than 1.2. We will consider the time at risk to be the time not spent in exacerbation (so that while a patient is in an exacerbation, they are not included as at risk for another).

A secondary analysis will define the at-risk time as the entire length of follow-up for the patient. Estimates will then be adjusted for sites, the stratification factors and other baseline covariates that are known to be strongly related to outcome (eg, age, smoking, bronchiectasis hospitalisations in year prior to trial—these will be prespecified in the Statistical Analysis Plan (SAP)).

We will undertake a sensitivity analysis by excluding those participants who have died. If there is any indication of a differential effect on deaths by treatment, we may consider models that allow the censoring to be informative. For participants who are lost to follow-up by 12 months, their information will be included in the statistical models up to the point that they are lost to follow-up. If loss to follow-up is higher than 10% we will conduct sensitivity analyses to investigate the impact.

We will also explore time to first exacerbation using a Cox regression, and a recurrent events analysis to allow for subsequent exacerbations. In addition, we will use mortality and hospitalisations due to bronchiectasis exacerbation data collected up until 24 months to extend the modelling beyond 12 months as a sensitivity analysis.

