#### Analysis of secondary outcome measures

The secondary outcomes: total number of bronchiectasis exacerbations requiring hospital admission, total number of emergency hospital admissions (all causes) will each be analysed as for the primary outcome described above. Disease-related health status (measured using the SGRQ, FEV_1_ and FVC) will be analysed using a mixed-effects model adjusted for site, stratification factors, patient characteristics and/or baseline clinical variables (to be pre-specified in the SAP). Random effects for patient will be included.

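### The exacerbation-free time at risk set for the primary outcome carries over to hospital admissions, where it does not fit; the primary yearly difference also needs a stated time base

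*Protocol article*

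**What the plan says.** All references are to the protocol article.

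- **Outcome.** Under Analysis of the primary outcome measure, the outcome is the "number of bronchiectasis exacerbations per participant requiring antibiotics over 12 months". It is analysed by negative binomial regression.
- **Superiority contrast.** The same section plans an absolute contrast: "The two-sided 95% CI for difference in mean number of exacerbations per year between the combination of LAMA/LABA and ICS/LAMA/LABA compared with placebo".
- **Time at risk.** The rule is "We will consider the time at risk to be the time not spent in exacerbation", and the reason given is "so that while a patient is in an exacerbation, they are not included as at risk for another".
- **Alternative denominator.** The article also plans one: "A secondary analysis will define the at-risk time as the entire length of follow-up for the patient".
- **Admissions.** Analysis of secondary outcome measures names exacerbations requiring admission and then says: "total number of emergency hospital admissions (all causes) will each be analysed as for the primary outcome described above". It gives no separate time at risk for either outcome.
- **Table 1** describes the first of these as a count of hospital admissions for exacerbations over the 12-month treatment period.

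**The concern.** The reason for removing exacerbation time is that a patient cannot start a new exacerbation while already in one. That reason does not extend to admissions. A patient in an exacerbation is still at risk of being admitted for it, and of an emergency admission for any other cause. The article does not say that admissions in that time are left out of the count, so they stay in the numerator while the time leaves the denominator. The arm with fewer or shorter exacerbations then has the larger denominator, and so the lower admission rate, even if treatment does nothing to admissions.

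The primary outcome has a separate, lesser problem of labelling. The outcome and the sample size are stated as numbers over a calendar year, but a model with this offset yields a rate per exacerbation-free year. If that rate is reported simply as a yearly difference, readers will compare it with the design difference although the time bases differ.

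**Working it through.** **Inputs.** The article gives placebo and active rates of 1.9 and 1.5 per year (Table 4, same relative differences), original planning rates of 2.4 and 1.9, and 240:240:120 participants with 5% loss (Sample size calculations). Days per exacerbation, D, are not given; I assume 14 to 21 and show 7 to 28.

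**1. The plan's own figures use a calendar year.** Non-inferiority power = Φ(margin / √(2 × rate / n) − 1.645), with n = 0.95 × 240 = 228 per arm and one full year of exposure each:

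- Rate 1.9, margin 0.38: 0.38 / 0.1291 − 1.645 = 1.298, giving 90.3%.
- Rate 1.4, margin 0.38: 0.38 / 0.1108 − 1.645 = 1.784, giving 96.3%.
- Rate 1.5, margin 0.30: 0.30 / 0.1147 − 1.645 = 0.970, giving 83.4%.

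All three match Table 4, so its rates are per calendar year.

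**2. Effect of the denominator.** Days at risk = 365 − rate × D. For admissions with no true effect (equal numbers per calendar year in both arms), the ratio of active to placebo is days at risk on placebo divided by days at risk on active. For the primary outcome, rate per exacerbation-free year = rate × 365 / days at risk.

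| D (assumed) | Days at risk, placebo / active | Admission ratio, truth 1 | Primary rates per exacerbation-free year | Difference (calendar 0.40) |
|---|---|---|---|---|
| 7 | 351.7 / 354.5 | 0.992 | 1.972 v 1.544 | 0.427 |
| 14 | 338.4 / 344.0 | 0.984 | 2.049 v 1.592 | 0.458 |
| 21 | 325.1 / 333.5 | 0.975 | 2.133 v 1.642 | 0.492 |
| 28 | 311.8 / 323.0 | 0.965 | 2.224 v 1.695 | 0.529 |

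At 14 to 21 days the primary difference reads 14% to 23% above the calendar-year value. The primary rate ratio moves less, from 1.5/1.9 = 0.789 to 0.777 and 0.770. With 2.4 v 1.9 and 14 days, the admission ratio is 331.4 / 338.4 = 0.979.

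**3. Admission shift against sampling error.** If admissions were as frequent as 1.9 per year and Poisson, with 114 placebo and 228 active participants, the standard error of the log ratio would be √(1/216.6 + 1/433.2) = 0.083. The shifts are 0.016 and 0.025 on the log scale, or 0.2 to 0.3 standard errors. Rarer admissions or overdispersion would make that fraction smaller.

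**4. Effect on the primary tests.** I simulated trials with 2.4 exacerbations per year in both arms, 114 v 228 participants, a common fixed duration of 14 or 21 days, dispersion 0, 0.5 or 1, and 400 runs per setting. The upper limit fell below 0 in 1.5% to 3.3% of runs with the at-risk offset and in 1.0% to 2.5% with the full-year offset (nominal 2.5%). For non-inferiority, a calendar ratio of 1.20 (1.9 per year in the reference arm) becomes 1.22 at 14 days, so that test is not made easier.

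**5. A treatment that only shortens exacerbations.** Hold the onset rate at 2.133 per exacerbation-free year in both arms. Calendar count = 2.133 / (1 + 2.133 × D/365): 1.90 at 21 days and 1.97 at 14 days. The planned offset gives a ratio of 1.00; a full follow-up offset gives 1.97 / 1.90 = 1.04.

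**The case against.** The carry-over is a reading of the text. Analysing admissions like the primary may mean only the same regression model, and offsets for single outcomes are often settled in the SAP, which is not shown. Taken literally, the sentence also carries over the full follow-up secondary analysis. For exacerbations requiring admission, the events are a subset of exacerbations and start in time at risk, so the exclusion can be defended there. The numerical effect is also small beside the precision of an admissions comparison.

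Much of this stands. It places the weight on all-cause emergency admissions, and on the first outcome only if admissions themselves are counted, as Table 1 has it. But the article's own description of the primary analysis includes the time-at-risk rule, and even on the literal reading full follow-up would be only the secondary version for admissions.

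A reader might go further and infer that the primary analysis itself is biased and that its two offsets should be exchanged. The article does not support that. Excluding exacerbation time is a recognised convention, a reason is given, the alternative is already planned, and type I error is not materially affected (step 4).

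A reader might also infer that a treatment which merely shortens exacerbations would seem to reduce their number. With equal counts of 1.9 and durations of 14 v 21 days, the planned offset does give 325.1 / 338.4 = 0.96. But equal counts over more time at risk mean that the onset rate really is lower. With an unchanged onset rate the planned offset gives 1.00, and it is full follow-up that departs from 1 (step 5).

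**Conclusion.** The point holds for admissions. Read literally, the plan gives them a denominator that omits time in which they can occur. With no true effect on admissions, the ratio would be about 0.984 to 0.975, a small bias towards the arm with fewer or shorter exacerbations. This rests on 1.9 v 1.5 exacerbations per year, an assumed 14 to 21 days each, equal admission numbers per calendar year, and the literal reading of the carry-over.

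For the primary outcome, what remains is a mismatch of time base between the modelled rate and the 12-month count on which the outcome and sample size are defined. The difference would read 0.46 to 0.49 in place of 0.40 only if it is reported without conversion, and the article does not say whether it will be converted. The choice of primary offset is not an error.

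**What to change.** **Admissions.** Under Analysis of secondary outcome measures, and in the SAP, state that the offset is entire follow-up time, to death, withdrawal or 12 months. This matters most for all-cause emergency admissions. The only downside is that the offset then differs from the primary's, which one sentence can explain.

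**Primary outcome.** Keep the prespecified at-risk offset and the planned full follow-up secondary analysis. Report the absolute difference as a 12-month, calendar-year mean, or label it as per exacerbation-free year.

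Both changes are matters of wording. They need no new data, and the article has the SAP agreed before any analysis is run.

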## Introduction

Bronchiectasis is a chronic lung condition, characterised by dilated bronchi, leading to symptoms of breathlessness and chronic productive cough, with intermittent infective exacerbations. Bronchiectasis has various potential aetiologies including immune-deficiency syndromes, allergic bronchopulmonary aspergillosis, chronic obstructive pulmonary disease (COPD), ciliary dysfunction and postinfectious, yet studies have found that between a quarter and half of cases are idiopathic.^1 2^ Patients often have recurrent, costly hospital admissions, a poorer quality of life^3 4^ and clinically significant fatigue.^5 6^

Current estimates suggest a prevalence of 100 000 adult patients with the condition in the UK. Importantly, studies demonstrate that up to 50% of patients with COPD have coexistent bronchiectasis.^7^ With approximately 1 000 000 patients with COPD in the UK,^8^ there is potential for a significant increase of case-finding of COPD-associated bronchiectasis over the coming years.

Bronchiectasis mortality rates are approximately 50% higher than that of uncomplicated COPD (calculated at 3% per annum) and have been reported to be increasing.^9^ Prognosis varies, with a prior study of 91 patients^10^ finding that the primary cause of death was usually respiratory, with survival rates of 91% at 4 years and 68.3% at 12.3 years. The same study found factors such as chronic infection with *Pseudomonas aeruginosa* increase mortality.

Multicentre data suggest that the Bronchiectasis Severity Index (BSI), a multicomponent clinical scoring system, is useful in predicting both mortality and morbidity (hospitalisation). This score was validated in 1300 patients across Europe.^11^

Infective exacerbations lead to significant morbidity. Within the UK national audit data patient group, average exacerbation rate is approximately 3 per year (nearly twice the rate of COPD) with an attendant risk of hospitalisation. This is consistent with published American data on the increasing burden of bronchiectasis^12^ and in the UK.^13^ Previously published UK data also emphasise the burden of bronchiectasis, uncertainties in aetiology and lack of evidence for the treatments that are often used.^14^ Hence, improved interventions in bronchiectasis are urgently required.

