For the primary superiority hypothesis, statistical analyses will be according to the intention to treat principle with a per protocol analysis performed as a sensitivity analysis. The per protocol analysis will exclude participants who were not compliant (at less than 75%) with their trial medication or who had a major protocol violation (to be pre-specified in the SAP).

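### The only firm analysis for deaths excludes everyone who died, which conditions on survival and cannot show whether the primary result withstands informative censoring

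*Protocol article*

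**What the plan says.** All of the following comes from the protocol article.

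- The primary outcome, the "number of bronchiectasis exacerbations per participant requiring antibiotics over 12 months", "will be compared between randomised groups using negative binomial regression adjusted for stratification factors" (Analysis of the primary outcome measure).
- Deaths: "We will undertake a sensitivity analysis by excluding those participants who have died". The next sentence adds: "If there is any indication of a differential effect on deaths by treatment, we may consider models that allow the censoring to be informative".
- Participants lost to follow-up: "their information will be included in the statistical models up to the point that they are lost to follow-up". Under Discontinuation and withdrawal, data collected before a participant withdraws are likewise kept and analysed.
- For superiority, "statistical analyses will be according to the intention to treat principle".
- Mortality (Introduction): "Bronchiectasis mortality rates are approximately 50% higher than that of uncomplicated COPD (calculated at 3% per annum", and, from a cohort of 91 patients, "survival rates of 91% at 4 years and 68.3% at 12.3 years".

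**The concern.** Death is a post-randomisation event, and the article itself ties it to the outcome. The Abstract associates recurrent exacerbations with a higher risk of death, and the Introduction says that deaths in the cited cohort were mostly respiratory. Removing those who died therefore compares survivors with survivors, and randomisation does not protect that comparison.

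The exclusion also sits badly beside the plan's other rules. Loss to follow-up and withdrawal keep the data already collected. For death, the check throws those data away.

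Finally, it does not answer the question that a check on deaths should answer. If death censors follow-up informatively, the unknown is what would have happened in the time not observed. Deleting the participants concerned gives no information on that. Agreement with the primary result could then be taken for robustness that had not been tested.

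**Working it through.** The plan states no figure for this point, so there is none to reproduce. The check has three parts.

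**1. How many deaths to expect.** The cohort survival figure gives 1 − 0.91^(1/4) = 2.3% a year. The 3% a year may refer to bronchiectasis, or to COPD, in which case bronchiectasis is 3% × 1.5 = 4.5%. With the planned 600 participants, 120 of them on placebo, and equal mortality in all arms:

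| Annual mortality | Deaths in 600 | Deaths in 120 placebo |
|---|---|---|
| 2.3% | 14 | 2.8 |
| 3% | 18 | 3.6 |
| 4.5% | 27 | 5.4 |

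**2. How far exclusion moves the rate ratio.** This used a simulation of 900,000 participants (placebo to active 1:2) in weekly steps over 12 months.

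- From Sample size calculations: rates of 2.4 and 1.9 a year, so a rate ratio of 1.9/2.4 = 0.79.
- Assumed, not in the article: dispersion 0.6, a death hazard ratio (active v placebo) of 1 or 0.5, and four mechanisms linking death to exacerbations.
- Model: negative binomial with log follow-up time as offset. All time alive counted as time at risk, which is simpler than the plan's primary definition.
- Benchmark: the rate ratio from the same participants' full-year counts had nobody died.

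Deviation from the benchmark at 4.5% placebo mortality and death hazard ratio 0.5:

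| Mechanism | Data kept to death | Deaths excluded |
|---|---|---|
| Each exacerbation carries a risk of death | 0.000 | +0.020 |
| Shared frailty (hazard proportional to a participant's underlying rate) | +0.004 | +0.010 |
| Death unrelated to exacerbations | 0.000 | 0.000 |
| Extra exacerbations just before death (mean of one) | −0.009 | 0.000 |

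A repeat run with a new random seed gave the same pattern. Simulation error is about 0.001.

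Other settings:

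- First mechanism, excluding deaths: +0.011 at 2.3% mortality and hazard ratio 0.5; +0.003 to +0.004 at hazard ratio 1 (2.3% to 4.5% mortality).
- Shared frailty with hazard ratio 1: both approaches are within about 0.001 of the benchmark.
- An assumed 10% mortality, well above the cited figures, with hazard ratio 0.5: exclusion shifts the ratio by +0.022 (frailty) to +0.043 (first mechanism).

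In the last row of the table, the verdict depends on the benchmark. The terminal exacerbations are real events, and keeping data to death counts them; the benchmark without deaths does not.

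**3. The shift against the trial's precision.** After 5% loss, 228 and 114 participants remain. The variance of the log rate ratio is 1/(n₁μ₁) + k/n₁ + 1/(n₀μ₀) + k/n₀, with k the dispersion.

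- Rates 1.9 and 2.4, k = 0.6: 0.0023 + 0.0026 + 0.0037 + 0.0053 = 0.0139. The standard error is 0.118 on the log scale, and 0.79 × 0.118 = 0.09 on the ratio.
- Updated rates 1.5 and 1.9 (Table 4), k = 0.5 to 1: variance 0.0141 to 0.0207, so a standard error of 0.09 to 0.11 on the ratio.

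The largest shift at cited mortality is therefore 0.020/0.09, about a fifth of a standard error.

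**The case against.** The strongest reply is that this is one sensitivity analysis and little turns on it. The primary superiority analysis is by intention to treat, mortality is a separate secondary outcome, and Cox and recurrent-event analyses are also planned. The shift is small against the standard error. All of this stands, and it limits the weight of the point.

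A second reply is that the plan does provide for informative censoring. It does, but only as an option, and the trigger is not defined. A reader might infer that the trigger would fail because a difference in deaths cannot be detected. If it meant two-sided significance at 5%, Fisher's exact test would detect a halving of deaths with only 13% to 20% power (120 v 240) or 15% to 25% (120 v 480), at 2.3% to 4.5% placebo mortality. The article, however, asks for a mere indication of a difference, not significance. The trigger is loose, but it is not shown to fail, and its definition can properly be left to the SAP. The exclusion is different: it is a stated method, not a missing detail.

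A third reply concerns the remedy. With some 14 to 27 deaths, a joint model may be poorly estimated, and a tipping-point analysis posits exacerbations in time after death. Both are fair. The second is inherent in any check against a scenario without deaths, and the report should say so.

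**Conclusion.** The point holds and is minor. Excluding participants who died conditions on survival, breaks the randomised comparison, discards observed data and cannot assess informative censoring. That conclusion follows from the method and needs no simulation.

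A reader might go further and infer that exclusion always makes the bias worse. The documents do not support this. It adds bias, here towards a rate ratio of 1, when sicker participants die and deaths differ by arm: up to about +0.02 on 0.79 at 4.5% placebo mortality and a death hazard ratio of 0.5. With death unrelated to exacerbations the effect is nil. With exacerbations clustered just before death, exclusion lies closer to the benchmark without deaths. The article does not say which mechanism applies, and the dispersion and hazard ratio are assumptions.

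Nor do the documents support an inference that the trial's main conclusion is at risk. The primary analysis does not use the exclusion.

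**What to change.** Replace the exclusion sentence with two commitments.

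1. All randomised participants contribute their data up to death in every analysis of exacerbations.
2. A sensitivity analysis that retains them is run whatever the observed deaths by arm. The simpler choice is a tipping-point analysis that varies, separately by arm, the exacerbation rate assumed for the unobserved time after death, and reports where the conclusion would change. A joint frailty model for exacerbations and death is an alternative if the number of deaths supports it.

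The cost is one changed sentence and a little more analysis. Exacerbations and deaths are already collected, so no new data are needed. The drawback is that the check will be imprecise with few deaths.

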### Discontinuation and withdrawal

Participants are free to discontinue trial treatment or withdraw from the trial at any time without detriment to their care. Participants choosing to discontinue trial treatment will be invited to complete all trial follow-up visits and assessments. Participants choosing to withdraw from the trial will not take part in any further trial activity. Data collected up to the point of withdrawal will be retained and included in analysis. Participants withdrawn from the trial after they have been randomised will not be replaced.

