### Sample size calculations

The original sample size calculation was based on the number of exacerbations among a similar population in prior national audits.^15 23^ The average number of exacerbations was 2.3 per year. Restricting trial entry to those who had ≥3, the original inclusion criteria (assuming a Poisson distribution) gives an average of around 3.8. We therefore assumed, given Hawthorne effect and regression to the mean, that the placebo arm would have a lower mean exacerbation rate than this, and assumed a mean of 2.4 over 1 year. The sample size was chosen so that the trial was well powered to detect a clinically meaningful fall in mean exacerbation rates for bronchiectasis exacerbations to 1.9 year in LAMA/LABA and ICS/LAMA/LABA arms (approximately 20% reduction). This effect size is realistic when compared with the 20%–30% reduction seen in COPD trials with dual bronchodilators/triple therapy and is accepted as clinically meaningful. Although likely studying a different sub population in bronchiectasis, a recent inhaled antibiotic trial in bronchiectasis reduced exacerbations by 39%.^4^

For 90% power (two-sided 5% significance level) to conclude that LAMA/LABA is more effective than placebo with the above parameters, we have calculated (assuming large-sample approximation of the Poisson distribution) that a sample size of 600 participants is needed, randomised 240:240:120 between LAMA/LABA, ICS/LAMA/LABA and placebo. This allows for a 5% loss to follow-up. This represents a conservative retention rate compared with over 95% observed in the NIHR *HTA* TWICS study with similar pragmatic design and limited patient burden. This calculation assumes a difference between placebo and LABA/LAMA of 0.5 exacerbations per year (21% relative reduction).

If superiority of LAMA/LABA versus placebo is concluded, we will then test non-inferiority of LAMA/LABA against ICS/LAMA/LABA. The sample size will give 90% power (one-sided 5% type I error) with a 0.38 non-inferiority margin (reflecting 20% of the assumed LAMA/LABA rate).

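### The per protocol check is assigned to superiority only, so the powered non-inferiority test has no adherence-based check although dilution from non-adherence can favour it

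*Protocol article*

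**What the plan says.** All references are to the protocol article.

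- **Analysis sets** (Analysis of the primary outcome measure): "For the primary superiority hypothesis, statistical analyses will be according to the intention to treat principle with a per protocol analysis" in a supporting, sensitivity role. The set is then defined: "The per protocol analysis will exclude participants who were not compliant (at less than 75%) with their trial medication", together with those who had a major violation, which the SAP is to define.
- **Model** (same section): the exacerbation count "will be compared between randomised groups using negative binomial regression adjusted for stratification factors", and "This model will be used to compute CIs to test the superiority and non-inferiority hypotheses".
- **Non-inferiority rule** (same section): estimate the dual/triple incidence rate ratio (IRR) and "test whether the upper boundary of the two-sided 90% CI is lower than 1.2".
- **Status of the test** (Sample size calculations): it follows only if dual therapy is shown superior to placebo, and it is powered: "The sample size will give 90% power (one-sided 5% type I error) with a 0.38 non-inferiority margin". Table 4 gives it its own power column.
- **Follow-up after stopping** (Discontinuation and withdrawal): "Participants choosing to discontinue trial treatment will be invited to complete all trial follow-up visits and assessments".

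No section names an analysis set for the non-inferiority test.

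**The concern.** For superiority, an intention-to-treat (ITT) comparison is the cautious one, because non-adherence shrinks a real difference and makes success harder. For non-inferiority the same shrinkage can help. Participants who stop the inhaler stay in follow-up, and their off-treatment exacerbations count in the randomised arm. If both active arms lose a similar share and do not differ once off treatment, the dual/triple ratio is pulled towards 1 and away from the 1.2 limit.

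The article therefore attaches its adherence check to the hypothesis that needs it less and leaves it off the one that needs it more. A non-inferiority result would be read as evidence that adding ICS brings no important further reduction in exacerbations. Poor adherence should not make that conclusion easier to reach without the reader being able to see it.

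**Working it through.** **Inputs from the article.** 240 per active arm and 120 on placebo, less 5% loss: 228, 228 and 114. Table 4 rates: 2.4 and 1.9 originally; 1.9 and 1.5 with the same relative difference. Limit 1.2 with a two-sided 90% CI. Gate: dual superior to placebo, two-sided 5%.

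**Assumptions, not in the documents.** Share off treatment d = 10, 20 or 30%, equal in both active arms; no difference between the arms off treatment; negative binomial dispersion k = 0 (Poisson) or 0.5; true on-treatment IRR exactly 1.2, so that non-inferiority is false.

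**1. The plan's own figure.** Power = Φ(margin / √(2 × rate / n) − 1.645), n = 228.
- Rate 1.9, margin 0.38: √(3.8/228) = 0.1291; 0.38/0.1291 = 2.943; Φ(1.299) = 90.3% (stated 90.3%).
- The other two Table 4 rows give 96.3% and 83.4%, as stated.

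**2. Dilution.** Diluted rate = (1 − d) × on-treatment rate + d × off-treatment rate.
- Scenario A: placebo 1.9, triple 1.5, dual 1.2 × 1.5 = 1.8, off-treatment rate equal to triple. Dual becomes 1.77, 1.74, 1.71; IRR 1.18, 1.16, 1.14.
- Scenario B: placebo 1.9, dual at its planned 1.5, triple 1.5/1.2 = 1.25, off-treatment rate equal to placebo. Dual becomes 1.54, 1.58, 1.62 and triple 1.315, 1.38, 1.445; IRR 1.171, 1.145, 1.121.

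**3. Chance of meeting the 1.2 rule, ignoring the gate.** P = Φ((ln 1.2 − ln IRR)/SE − 1.645), with SE² = (1/dual + k)/228 + (1/triple + k)/228. Example, A at 20%, k = 0: SE² = (0.5747 + 0.6667)/228, SE = 0.0738; (0.1823 − 0.1484)/0.0738 = 0.459; Φ(−1.186) = 11.8%.

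**4. With the gate.** 400,000 simulated trials per setting, counting those that pass dual versus placebo superiority and then meet the 1.2 rule.

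| Scenario | k | Ungated, d = 10/20/30% | Gated, d = 10/20/30% |
|---|---|---|---|
| A | 0 | 7.8 / 11.8 / 17.0% | 2.6 / 4.5 / 7.3% |
| A | 0.5 | 7.0 / 9.6 / 13.0% | about 2 / 3 / 4% |
| B | 0 | 9.1 / 15.0 / 22.7% | 8.0 / 11.8 / 14.8% |
| B | 0.5 | 7.9 / 11.9 / 16.7% | 5.5 / 6.9 / 7.7% |

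The gate does most in A, because dual at 1.8 against placebo at 1.9 seldom passes. In B dual has its planned effect, so the gate passes more often (65.5, 54.9 and 44.0% at k = 0) and gives only partial protection. If the off-treatment rate in A is the placebo rate, the gated figures are about 2 to 3%. With the original rates (2.4, 1.9 and 1.9/1.2 = 1.583, off-treatment rate equal to placebo) they are 8.9, 14.3 and 18.8% at k = 0, and 6.0, 7.5 and 8.7% at k = 0.5.

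**5. Precision of a per protocol analysis.** Equal rates of 1.5, k = 0, IRR scale.
- 228 per arm: SE = √(2/(1.5 × 228)) = 0.0765; 0.1823/0.0765 = 2.384; Φ(0.739) = 77%.
- 20% excluded, 228 × 0.8 ≈ 182 per arm: SE = 0.0856; Φ(0.485) = 69%.
- At k = 0.5 the two figures are about 56% and 49%.

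The starting 77% is below Table 4's 83.4% because Table 4 uses an absolute margin while the decision rule uses the ratio. That gap is not a cost of the per protocol analysis.

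**The case against.** **Silence is not error.** The article never says that non-inferiority will rest on ITT alone, and restricting the sentence to superiority may mean that non-inferiority is handled elsewhere. The article condenses protocol version 6.0 and says a SAP governs all analyses. This stands in part: a reader might infer that the trial has excluded a per protocol analysis of non-inferiority, and the text does not support that. But the article does address analysis sets. It fixes them for one of two powered hypotheses, defines the per protocol set, and defers only the definition of a major violation. With one model between randomised groups serving both hypotheses, ITT is the natural default for the other.

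**The gate protects.** A reader might infer that the false-positive rate becomes 7 to 17%. Those are the ungated Scenario A figures. Non-inferiority is tested only after superiority, and with the gate the same scenario gives about 2 to 7%, mostly below 5%. This objection stands for that scenario. It does not dispose of the point, because gated inflation remains when dual therapy has its planned effect.

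**The trial is pragmatic.** A comparison as randomised is a legitimate target. The per protocol set breaks randomisation and still admits participants with up to 25% of doses missed, so it is neither unbiased nor free of dilution. This stands. It counts against making success in both sets a condition for claiming non-inferiority, which a reader might take to be the only acceptable rule. It does not count against reporting both.

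**The direction is conditional.** Unequal stopping between the active arms could move the ratio either way. This stands, and is why the point is stated for similar stopping.

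**Conclusion.** The point holds in a limited form. The per protocol analysis is tied to superiority, and the gated, powered non-inferiority test has no stated adherence-based check and by default compares randomised groups. Under similar stopping and no off-treatment difference, dilution favours meeting the 1.2 rule.

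At the updated planning rates, with a true on-treatment IRR of 1.2 and 10 to 30% off treatment, the gated chance of a false conclusion is about 2 to 7% in Scenario A and about 6 to 15% in Scenario B, against 5% nominal. The range is wide because non-adherence, dispersion and off-treatment rates are all assumed. The direction is better established than the size. The documents support neither a claim that the error rate is inflated in every scenario nor a claim that an ITT non-inferiority result would be invalid.

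**What to change.** Add to the primary analysis section, or confirm in the SAP before any analysis, that:

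- the dual versus triple non-inferiority comparison will be analysed in both the ITT set and the per protocol set already defined;
- both IRRs with two-sided 90% CIs will be reported against 1.2;
- non-inferiority will be described as robust only if the two are consistent, and disagreement will be reported as such.

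This needs a few sentences and one further run of a model already planned. The price is a possibly less favourable conclusion: the per protocol set is smaller (power about 77% falling to 69% if 20% per arm are excluded, with no overdispersion) and is not protected by randomisation. A per protocol interval that crosses 1.2 may therefore reflect lost precision or selection rather than a real difference, and the report should say so.
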